#### **4.2 Measures**

The primary outcomes for this study will be toe brachial index, measured pre-dialysis, during dialysis (at 1, 2, and 3 hours), and post-dialysis.

Additional measures will include routinely collected clinical data:

- each timepoint: ultrafiltration (fluid-removal) rate, and dialysis blood flow rate

[figure not shown]

- Each session: pre- and post-dialysis weight, requirement for fluid bolus for symptomatic intradialytic hypotension
- Each subject – demographic data, history of current ulceration, prior amputation, prior ulceration, PVD, revascularization for PVD, diabetes, diagnosed peripheral neuropathy.

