#### Details of data collection, processing and analysis :

Patients attending NH dialysis service will be approached over six months until 30 participants are recruited. The PI or research assistant will only approach those patients who are determined by the dialysis nurses as being clinically appropriate to participate based on the inclusion criteria. Written, informed consent will be obtained prior to each assessment by a study investigator who is an employee of NH (BB).

TBIs will be completed on each participant pre-dialysis, at hourly intervals during dialysis, and post-dialysis.

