### 4.4 STATISTICAL CONSIDERATIONS

The sample size has not been able to be guided based on published information, as no details relating to the variance from patient to patient in the change in toe brachial indices over time can be found. Stern (2014) indicates that the pre-dialysis and post-dialysis systolic

blood pressure are found to be 10 mm Hg more and 10 mm Hg less than the interdialytic blood pressure respectively [13], but there is no indication of the variance from patient to patient in the change in toe brachial indices over time. Thus, the sample size of n=30 patients has been selected as being able to be conducted effectively within the timeframe of the study. This will then indicate if additional sample is required to address the needs of the study.

Descriptive analysis will be conducted to summarise the toe brachial index results over the study timepoints for each patient. Data will be presented as means (standard deviations) if normally distributed or as median (inter-quartile ranges) if skewed. The mean of changes from one timepoint to the next are likely to be normally distributed, and thus the data will be assessed using paired t-tests. More detailed analysis, including longitudinal analysis using mixed-effects linear regression models may be explored if the sample size allows an investigation of the effects of some patient characteristics. A p-value of less than 0.05 will indicate statistical significance, with the data to be compiled in Microsoft Excel and analysed using Stata version 15.1 (StataCorp, College Stations, Texas, USA).

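### Section 4.4 commits only to paired t-tests on successive changes and leaves the mixed model optional, so missed readings would cost pairs and could bias the TBI change in an unknown direction

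*Protocol*

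**What the plan says.** Section 4.2 sets the primary outcome as "toe brachial index, measured pre-dialysis, during dialysis (at 1, 2, and 3 hours), and post-dialysis", which is five readings per patient. Under the data-collection heading in section 4.3, full measurement is planned: "TBIs will be completed on each participant pre-dialysis, at hourly intervals during dialysis, and post-dialysis".

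Section 4.4 names one committed inferential method, the paired t-test: "The mean of changes from one timepoint to the next are likely to be normally distributed, and thus the data will be assessed using paired" (the quote stops just before the name of the test). The threshold is set as follows: "A p-value of less than 0.05 will indicate statistical significance". The repeated-measures model is only a possibility: "longitudinal analysis using mixed-effects linear regression models may be explored if the sample size allows an investigation of the effects of some patient characteristics". Its stated purpose is patient characteristics, not the time course itself.

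The sample size is a feasibility choice: "the sample size of n=30 patients has been selected as being able to be conducted effectively within the timeframe of the study". The reason given is that "there is no indication of the variance from patient to patient in the change in toe brachial indices over time". The protocol states no rate of missed readings and no allowance for them.

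The Background (section 2) expects that pressure may fall or rise during dialysis. Section 4.2 lists "requirement for fluid bolus for symptomatic intradialytic hypotension" among the session data. Neither section connects these events with missed TBI readings.

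**The concern.** A paired t-test uses only patients who have both readings of the pair. With five timepoints and any gaps, each test may rest on a different subset, and a patient's other readings contribute nothing to a comparison in which one member is missing. If the chance of a gap depends on how TBI has been moving, the remaining pairs are a selected group.

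The analysis that uses all readings is the mixed model, and section 4.4 makes it depend on whether the sample supports patient-characteristic effects. That condition suits covariates. It does not suit a model whose only fixed effect is timepoint.

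The Introduction says the results will bear on whether TBI can suitably be measured during dialysis, and that such assessments guide debridement and dressing choices. That question calls for each intradialytic and post-dialysis reading to be compared with pre-dialysis. Successive changes do not make that comparison directly beyond the first hour, and the change from pre-dialysis is where selective loss of readings can matter most.

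**Working it through.** **Inputs from the protocol.** 30 patients; five readings each (section 4.2); significance at 0.05 (section 4.4; two-sided assumed). The SD of change, the correlation between changes and the missing rate are not given, so everything below that uses them is an assumption. The sample size has no stated effect size, SD or power, so there is no figure to reproduce.

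**1. Feasibility of a time-only model.** 30 × 5 = 150 planned readings. Timepoint as a factor takes 5 mean parameters. An unstructured covariance takes 5 × 6 / 2 = 15 more. This is feasible with 30 patients.

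**2. Cost of lost pairs.** Smallest standardized paired change detectable with a two-sided 0.05 t-test (noncentral t), in SDs of the change:

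| Pairs | 80% power | 90% power |
|---|---|---|
| 30 | 0.53 | 0.61 |
| 27 (10% lost) | 0.56 | 0.65 |
| 24 (20% lost) | 0.60 | 0.69 |
| 21 (30% lost) | 0.64 | 0.74 |

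**3. Illustrative bias, missing at random (MAR).** Assume the true change from pre-dialysis is μ = −0.05 at both 2 h and 3 h, with SD σ = 0.10 and correlation ρ = 0.7 between the two changes. The 3 h reading is missing in the fraction p with the largest 2 h fall. For a normal distribution with its lowest p removed, the retained 2 h mean shifts up by σ·φ(z_p)/(1 − p), and the retained 3 h mean by ρ times that.

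- p = 0.20: shift at 2 h = 0.10 × 0.280 / 0.80 = 0.035; at 3 h = 0.7 × 0.035 = 0.0245. Paired pre-to-3 h estimate = −0.05 + 0.0245 = **−0.0255**. Adjacent 2-to-3 h estimate = −0.0255 − (−0.05 + 0.035) = **−0.0105**, against a truth of 0.
- p = 0.10: shift at 2 h = 0.10 × 0.1755 / 0.90 = 0.0195; at 3 h = 0.7 × 0.0195 = 0.0137. Paired pre-to-3 h estimate = **−0.036**. Adjacent estimate = −(1 − 0.7) × 0.0195 = **−0.006**.

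A simulation of 2,000,000 pairs gave −0.0255 and −0.0104 at 20%, and −0.0363 for pre-to-3 h at 10%. An estimate that also uses the 2 h readings returned −0.0501 and −0.0500.

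Range: the bias is ρσφ(z_p)/(1 − p) and does not depend on μ. At p = 0.20 and σ = 0.10 it runs from 0 (ρ = 0) to 0.035 (ρ = 1) for pre-to-3 h, and from −0.035 to 0 for the adjacent change. If the largest risers were missing instead, the signs reverse: at 20% the pre-to-3 h estimate would be −0.05 − 0.0245 = −0.0745.

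**4. Second illustration, several mechanisms.** Five timepoints were simulated with 400,000 patients per scenario. The assumptions were: intercept SD 1, mean slope −0.1 per timepoint, slope SD 0.15, residual SD 0.3; only the post reading missing, with log-odds 1 per SD of change. The true pre-to-post change is −0.40. With readings missing completely at random, the paired estimate was about −0.40 at every rate. Otherwise:

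| Post missing | Paired, MAR, decliners missing | Paired, MAR, risers missing | Paired, not at random (MNAR), decliners missing | Likelihood estimate, same MNAR |
|---|---|---|---|---|
| 5% | −0.375 | −0.427 | −0.367 | −0.391 |
| 10% | −0.347 | −0.454 | −0.335 | −0.378 |
| 20% | −0.299 | −0.501 | −0.274 | −0.356 |
| 30% | −0.254 | −0.546 | −0.214 | −0.334 |

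Under both MAR columns the likelihood estimate was −0.40 throughout.

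For the last adjacent change (3 h to post, truth −0.10), the paired estimate over 5–30% missing was −0.103 to −0.110 under MAR with decliners missing, and −0.099 to −0.091 with risers missing. Under MNAR it was −0.090 to −0.039. The likelihood estimate did no better there, at −0.090 to −0.034.

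**The case against.** The strongest reply is that nothing in the protocol says readings will be missed. Section 4.3 plans every reading on every participant around a dialysis session, with no long follow-up. Listing fluid boluses as a measure suggests, if anything, that these patients stay under observation. With complete data, paired t-tests are valid and the model gives the same mean changes. This stands, and it makes the bias conditional.

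A reader might infer that the change is biased toward stable patients, and hence toward finding TBI during dialysis suitable. The documents do not support that. TBI is toe pressure over brachial pressure, so a fall in brachial pressure can raise it, lower it or leave it unchanged. The Introduction says the effect of dialysis on toe pressure is unknown, and the Background describes both hypotension and hypertension.

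A reader might also infer that the estimate would be halved. That ratio depends on the assumed −0.05 and applies to the change from pre-dialysis, not to the successive changes that section 4.4 names. For those, the MAR bias is small and, with decliners missing, away from zero. Nor does a patient with one missed reading leave the whole analysis; only the pairs that use that reading are lost.

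Two further points have force. A likelihood model removes the bias only under MAR. And section 4.4 already links the sample-size condition to patient characteristics, while missing-data detail may sit in an SAP that is not shown. Even so, the stated text commits to one method and makes the other optional as a whole, with no separate commitment to a time-only model.

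**Conclusion.** The point holds in conditional form. Section 4.4 fixes pairwise-complete t-tests on successive changes as the only committed test and leaves optional a model that 30 patients with five readings each can support. If readings are missed for reasons related to TBI, pairs are lost and the estimates could be biased in a direction that cannot be fixed in advance.

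The size rests wholly on assumptions. In the first illustration, with 10–20% missing, a true pre-to-3 h change of −0.05 is estimated as −0.036 to −0.026, and the adjacent change is off by about −0.006 to −0.01. In the second, with decliners missing at 5–30%, the pre-to-post change shrinks by about 7–37% under MAR and 9–47% under MNAR; with risers missing it is exaggerated instead. If no readings are missed, or they are missed completely at random, there is no bias. No figure in the protocol is contradicted. This is a cheap improvement to a stated choice, not an error that invalidates the study.

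**What to change.** In section 4.4, make the main analysis a linear mixed model fitted by REML to all available readings, with time as a five-level factor, an unstructured within-patient covariance (and a simpler structure named in advance in case it does not converge), and small-sample degrees of freedom such as Kenward-Roger. Report contrasts of each later timepoint against pre-dialysis. Keep the paired t-tests as a sensitivity analysis. Apply the sample-size condition only to patient-characteristic terms. Recording the reason for any missed reading would help to judge whether MAR is plausible.

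The cost is a little more analysis work, with no extra patients or measurements. With complete data the estimated mean changes are unchanged. The model is not a full safeguard: under MNAR it reduced the bias in the change from pre-dialysis but did not remove it, and it did not help the last adjacent change in the illustration above.

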**1. INTRODUCTION**

Current standard practice for lower limb arterial assessment to determine the presence of peripheral arterial disease includes the use of a toe brachial index (TBI), whereby the toe systolic blood pressure is divided by the brachial systolic blood pressure. Anecdotal evidence suggests that due to patient convenience clinicians often assess TBIs during haemodialysis. Historically this has not taken into consideration the fact that those with CKD on haemodialysis can experience changes in their systolic blood pressure during dialysis, which is known as intradialytic hypertension and intradialytic hypotension. These changes may in turn affect the results of toe brachial index.

Currently it is not known if dialysis affects toe systolic pressures. This study will aim to monitor both brachial and toe systolic blood pressures to obtain TBI results, with measurements taken at specific time intervals (pre-dialysis, during dialysis (hourly) and post-dialysis) to monitor the association between the two. These results may then be applied to clinical practice to determine the suitability of completing TBI assessments during dialysis. This information will guide clinical practice, as these assessments guide decisions regarding sharp debridement, and wound dressing selection.

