The ABI has been shown to be both specific and sensitive in the diagnosis of PAD (Hinchcliff et al., 2019) however in some patients it may yield a falsely elevated result due to the presence of medial artery calcification, a condition common to people in the advanced stages of both diabetes and CKD. In this case, it is preferable to measure toe systolic pressure and conduct a TBI. There is no single measure that has been shown to provide an optimal assessment of risk of PAD, however PAD is less likely when an ABI is between 0.9-1.3; toe pressure measurements are higher than 30mmHg; or when a TBI is higher than 0.75, and Doppler waveforms are triphasic. Using more than one of these tests in parallel enables clinicians to make a more accurate diagnosis. Recent research has suggested that the use of pedal Doppler arterial waveforms in combination with TBI is the superior lower limb arterial assessment (Brownrigg et al., 2016). Clinical guidelines recommend that patients undergoing ABI, TBI and audible doppler assessments are seated for at least 20 minutes prior to assessment (Hinchcliff et al., 2019).

Expert evaluation for PAD including use of TBI is also standard-of-care in the management of foot ulcers in high-risk patients such as those with ESKD. PAD can alter the body's ability to heal a foot ulceration, and can lead to infection, increased tissue loss and insufficient delivery of nutrition, oxygen and antibiotics, all of which can lead to further foot amputation (Amin and Doupis, 2016). The presence of PAD needs to be promptly excluded so that clinicians can safely perform adequate ulcer treatment including sharp debridement to assist with wound preparation. It is also necessary to have this information in order to decide whether a dry or moist wound dressing is suitable to treat a DFU (Roelsing and Andrews, 2019).

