Due to the great demands on patient times of haemodialysis, it is common for podiatry assessment and treatment to occur opportunistically during dialysis sessions. However, there has been no systematic evaluation of the impact of haemodialysis and in particular changes in blood pressure during dialysis may affect the measurement of TBI. Blood pressure is routinely measured before, during and after haemodialysis and patients may experience an fall in blood pressure during or immediately after haemodialysis known as intradialytic hypotension (Sars B et al., 2020) or a paradoxical increase in blood pressure known as intradialytic hypertension (Van Buren and Inrig, 2016). Pre-dialysis systolic blood pressure is typically around 10mmHg higher than intradialytic blood pressure and post-dialysis systolic blood pressure is around 10mmHg less than intradialytic blood pressure (Sterns et al., 2014). When intradialytic hypertension occurs, it is most common in the second or third hour of hemodialysis, and after significant ultrafiltration has taken place (Inrig, 2009). During dialysis blood is also diverted to an extracorporeal circuit, which may result in contraction of blood vessels to maintain blood pressure.

The results of this research will aim to assist clinicians with clinical guidelines around arterial assessments and also wound management for those undergoing haemodialysis.

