### **3. AIM(S) AND OBJECTIVES OF STUDY**

The aim of this study is to evaluate toe brachial indices, during haemodialysis, in participants with end stage kidney disease.

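### The only committed inference, a paired t-test of mean change between consecutive timepoints, cannot show whether a TBI taken during dialysis is suitable for decisions on one patient

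*Protocol*

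**What the plan says.** The formal aim in section 3 is broad: "The aim of this study is to evaluate toe brachial indices, during haemodialysis, in participants with end stage kidney disease". The intended use is in section 1: "These results may then be applied to clinical practice to determine the suitability of completing TBI assessments during dialysis". The same section adds that "these assessments guide decisions regarding sharp debridement, and wound dressing selection".

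Section 4.2 makes TBI the primary outcome at five timepoints: pre-dialysis, 1, 2 and 3 hours, and post-dialysis. Section 4.4 then plans:

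- a descriptive summary of TBI across timepoints for each patient, as mean (SD) or median (IQR);
- paired t-tests on the change between consecutive timepoints, with this rule: "A p-value of less than 0.05 will indicate statistical significance";
- mixed models as an option, if sample size allows, to look at patient characteristics.

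The sample of 30 is a feasibility figure. Section 4.4 says that nothing is known about how much the change in TBI varies between patients. No reference timepoint, acceptable difference, agreement measure or count of patients changing category is given.

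**The concern.** Suitability for individual decisions depends on the spread of individual differences between an intradialytic TBI and the same patient's pre-dialysis TBI. A paired t-test asks whether the mean of those differences is zero. The two can part company in both directions: a mean near zero can sit on a wide spread, and a small, uniform, perhaps unimportant shift can be significant.

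The consecutive-timepoint structure adds a second gap. Of the four successive comparisons (pre to 1 h, 1 h to 2 h, 2 h to 3 h, 3 h to post), only the first sets an intradialytic reading against the pre-dialysis one.

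At stake is whether the study can deliver what section 1 wants from it. With p<0.05 as the only stated yardstick, the report would have no planned basis for saying whether intradialytic TBI is close enough to use.

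**Working it through.** **Inputs from the protocol.** n = 30 and alpha = 0.05 (section 4.4; two-sided assumed, as sidedness is not stated). The TBI value of 0.75 comes from section 2, where PAD is called less likely when, among other findings, "toe pressure measurements are higher than 30mmHg; or when a TBI is higher than 0.75". There is no power statement or margin, so the plan has no figure to reproduce.

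**Assumed inputs.** SD of individual change s = 0.05, 0.10, 0.15, 0.20 TBI units; baseline TBI normal with mean 0.60 or 0.75 and SD 0.20 or 0.25.

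**1. What the test can see.** If the true mean change is 0, the t-test is non-significant about 95% of the time at every s. This is 1 − alpha and needs no assumption about s, so the test cannot tell a small s from a large one.

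**2. What it can miss in the mean.** By the noncentral t distribution at n = 30, 80% power requires a mean change of 0.53 s.

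**3. Spread of individual change.** The 95% limits of agreement are mean ± 1.96 s. The 95% CI half-width of each limit is t(29) × s × √(1/30 + 1.96²/58) = 2.045 × 0.3155 × s = 0.645 s. With zero mean change, the share of patients changing by more than 0.10 is 2 × [1 − Φ(0.10/s)].

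| s | Mean change detectable with 80% power | Power if mean change is 0.05 | Limits of agreement | CI half-width of a limit | Share changing by >0.10 |
|---|---|---|---|---|---|
| 0.05 | 0.026 | about 100% | ±0.098 | 0.032 | 5% |
| 0.10 | 0.053 | 75% | ±0.196 | 0.065 | 32% |
| 0.15 | 0.079 | 42% | ±0.294 | 0.097 | 50% |
| 0.20 | 0.106 | 26% | ±0.392 | 0.129 | 62% |

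**4. Crossing 0.75 with zero mean change** (simulated, in either direction):

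| Baseline mean, SD | s = 0.05 | 0.10 | 0.15 | 0.20 |
|---|---|---|---|---|
| 0.75, 0.20 | 7.8% | 14.8% | 20.5% | 25.1% |
| 0.75, 0.25 | 6.3% | 12.1% | 17.1% | 21.4% |
| 0.60, 0.20 | 6.0% | 11.6% | 16.6% | 21.0% |
| 0.60, 0.25 | 5.2% | 10.2% | 14.8% | 18.8% |

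For a baseline mean of 0.75 the share has a closed form, arctan(s / baseline SD)/π. For example, arctan(0.05/0.20)/π = 0.078, which matches.

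**5. Two contrasting cases** (20,000 simulated studies of 30). If each patient shifts by +0.15 or −0.15 with equal chance, plus noise of SD 0.05, the test rejects in 5.1% of studies, in line with the nominal 5%. A uniform shift of 0.02 with SD 0.03 is significant in 94%.

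**6. Consecutive differences.** The 3 h minus pre-dialysis difference is the sum of three successive changes. Its mean is the sum of three means, but its SD also depends on how the changes correlate within a patient. Separate consecutive t-tests do not report that, so agreement at 2 h and 3 h cannot be recovered from them.

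**The case against.** The other side has real substance.

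- **Aim.** Section 3 only evaluates TBI. Suitability appears in section 1 as a possible later use, and section 4.4 expects the 30 patients to show whether more are needed. This stands, and it lowers the severity. It does not remove the mismatch: the spread of individual change is also what planning a larger sample would require.
- **Descriptives.** Per-patient summaries are planned, so individual variation is not hidden. This stands, but they have no reference timepoint and no criterion.
- **Left to an SAP.** Agreement statistics often are. Here, however, the protocol itself fixes the test and threshold, and these do not answer the use it states.

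Three stronger readings are tempting, and the protocol does not support them.

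- A reader might infer that p>0.05 will be reported as proof of suitability. No section says how a non-significant result will be read.
- A reader might infer that TBI shifts will cancel, because section 2 describes both a "fall in blood pressure during or immediately after haemodialysis known as intradialytic hypotension" and "a paradoxical increase in blood pressure known as intradialytic hypertension". Those are blood pressure changes. TBI is a ratio, section 1 says the effect of dialysis on toe pressure is unknown, and section 2 also gives a net average direction for systolic pressure. The point needs only spread between patients, not opposite shifts.
- A reader might take crossing 0.75 as a wound-care error. Section 2 uses that value to describe when PAD is less likely, alongside Doppler waveforms and with the caution that no single measure is optimal. It is not stated as a debridement or dressing threshold.

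**Conclusion.** The point holds as a should-fix. The committed inference addresses the average change between neighbouring timepoints, while the use in section 1 concerns how close one patient's intradialytic TBI is to that patient's pre-dialysis value. That mismatch is structural and depends on no assumed SD. A non-significant result in 30 patients would not support suitability, and the protocol supplies no other criterion.

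The size is illustrative only. With zero mean change, about 5% to 25% of patients would cross 0.75 over the assumed ranges (SD of change 0.05 to 0.20; baseline mean 0.60 to 0.75, SD 0.20 to 0.25). Part of any such crossing would be ordinary measurement error and not an effect of dialysis.

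**What to change.** In section 4.4:

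1. Name pre-dialysis TBI as the reference.
2. For each of 1, 2 and 3 hours, report the mean difference from pre-dialysis with its 95% CI, and Bland-Altman 95% limits of agreement with CIs. Read the limits against an acceptable TBI difference that the investigators set before analysis.
3. Report the number and percentage of patients changing side of 0.75, with exact 95% CI, labelled as a description and not a wound-care rule.
4. State that a non-significant mean change will not be taken as evidence of suitability.

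The cost is a few lines of text and agreement on a margin; the data are already being collected. Two limitations should be stated. Intervals are wide at n = 30: each limit carries about ±0.65 SD, and 5 of 30 patients crossing gives 5.6% to 34.7%. The protocol also describes no replicate pre-dialysis reading, so the limits will combine measurement error with any dialysis effect.

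### Four unadjusted paired t-tests on the five-timepoint primary outcome give a 17% to 19% chance of at least one false positive, with no overall test of time

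*Protocol*

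**What the plan says.** Protocol section 4.2 defines the outcome: "The primary outcomes for this study will be toe brachial index, measured pre-dialysis, during dialysis (at 1, 2, and 3 hours), and post-dialysis". That is five readings per patient, and none is ranked above the others.

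Section 4.4 chooses the paired t-test: "The mean of changes from one timepoint to the next are likely to be normally distributed, and thus the data will be assessed using paired" (the quote stops just short of the test's name). It then sets the threshold once, for everything: "A p-value of less than 0.05 will indicate statistical significance". The only analysis that would use all timepoints together is optional and has another purpose: "mixed-effects linear regression models may be explored if the sample size allows an investigation of the effects of some patient characteristics".

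The sample size has no power basis: "the sample size of n=30 patients has been selected as being able to be conducted effectively within the timeframe of the study". On variability the section says that "there is no indication of the variance from patient to patient in the change in toe brachial indices over time".

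**The concern.** Each t-test has a 5% chance of a false positive. A reader of the results will also want to know whether TBI changes across a dialysis session at all, and section 4.4 offers only four separate p-values to answer that. If an overall statement rests on whichever of the four falls below 0.05, its error rate is well above 5%.

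This matters because the Introduction expects the results to inform whether TBI should be assessed during dialysis, and says that such assessments guide debridement and dressing choice. A single chance finding among four could be taken as evidence that dialysis shifts the index.

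The protocol itself fixes both the test and the threshold, and the concern is what the two produce together. It is not a complaint about detail left to a statistical analysis plan.

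**Working it through.** **Inputs**
- Timepoints: 5 (section 4.2). Successive changes: 5 − 1 = 4.
- Threshold: 0.05 per test (section 4.4); two-sided is assumed, as the section does not say.
- Patients: 30 (sections 4.1 and 4.4), so each paired t-test has 29 degrees of freedom.
- Correlation between timepoints: not given. Assumed and varied: equal correlation (0.5, 0.8), first-order autoregressive (0.5, 0.7, 0.9), and a random walk (two step sizes).
- Normal data, complete for all patients, with no true change at any timepoint.

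**The plan's own figure.** There is none to reproduce beyond the per-test 0.05: no effect size, SD, power or overall error rate is stated.

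**Benchmark.** If the four tests were independent, the chance of at least one p<0.05 would be 1 − (1 − 0.05)^4 = 1 − 0.8145 = 0.1855.

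**Allowing for dependence.** Neighbouring changes share a reading, so the tests are correlated. Simulation of 100,000 null trials per structure gives this chance of at least one significant result among the four:

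| Assumed structure | Chance |
|---|---|
| Equal correlation 0.5 / 0.8 | 16.8% / 16.6% |
| Autoregressive 0.5 / 0.7 / 0.9 | 18.0% / 18.3% / 18.4% |
| Random walk, small / large steps | 18.4% / 18.6% |

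The range is about 17% to 19%, close to the benchmark, so the result depends little on the assumed structure.

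**After the fix**
- One joint test of the four changes (Hotelling's T², referred to F with 4 and 26 degrees of freedom) rejects in about 5% of null trials under the structures checked.
- Holm's procedure starts at 0.05/4 = 0.0125. Four independent tests at that level give 1 − (1 − 0.0125)^4 = 0.049, and the Bonferroni bound of 5% holds whatever the correlation.
- The joint test needs a small-sample reference distribution. If T² is instead compared with the chi-square critical value on 4 degrees of freedom (9.488), the equivalent F is 9.488 × 26/(4 × 29) = 2.127. On 4 and 26 degrees of freedom, F exceeds that 10.6% of the time.

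**Cost in sensitivity.** For a paired t-test with n = 30 and 80% power, the non-central t with non-centrality d√30 gives d = 0.529 at 0.05 (critical value 2.045) and d = 0.6447 at 0.0125 (critical value 2.663). That is about 0.53 and 0.64 SD of the change.

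**The case against.** **Purpose and size.** The stated aim is to evaluate TBI during dialysis. Section 4.4 opens with descriptive analysis, calls 30 patients a matter of feasibility, and expects the study to show whether more are needed. In such a study each interval's change can be reported as its own estimate, and strict control over the set of tests is partly a matter of preference. This stands, and it lowers the severity. It does not remove the point, because the protocol still declares a primary outcome and a significance rule and expects the results to be used in practice.

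**A later plan could settle it.** A statistical analysis plan could add an overall test or an adjustment. That is fair, but the rule as written carries no qualification.

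**Missed changes matter too.** Where the question is whether TBI can be trusted during dialysis, overlooking a real change may be as serious as a false alarm, and a stricter threshold makes that likelier. This stands as a cost. It is a reason to hold the joint test at 0.05 and to report confidence intervals for every change.

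**Stronger readings the text does not support**
- A reader might infer that all ten pairs of timepoints will be tested, for which the same simulation gives about 25% to 29%. Section 4.4 speaks only of successive changes, so that range is a hypothetical upper bound.
- A reader might infer that any one significant pair is to count as proof of a dialysis effect. The protocol states no such decision rule.
- A reader might conclude that one contrast must be made primary, such as the average of hours 1 to 3 against pre-dialysis. That average would leave out the post-dialysis reading, which section 4.2 includes in the primary outcome, and nothing in the protocol singles it out.

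**Conclusion.** The point holds for the four successive tests. With 30 patients and no true change, the chance of at least one p<0.05 is about 17% to 19%, more than three times the nominal 5%. The figure rests on assumed correlation structures, normal and complete data, and two-sided tests.

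The consequence is limited to an overall statement that TBI changes across dialysis. Each t-test, read alone as an estimate for its own interval, keeps its 5% level. The optional mixed model does not close the gap, because it is conditional and directed at patient characteristics. The change is worth making before the data are analysed, but severity is modest.

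**What to change.** In section 4.4:
1. First test the hypothesis of no change in mean TBI over the five timepoints with one joint test of time at two-sided 0.05. A repeated-measures mixed model with time as a five-level factor would serve, with small-sample degrees of freedom. So would Hotelling's T² if all readings are complete.
2. Then report the planned successive changes with confidence intervals and Holm-adjusted p-values.
3. Keep the mixed models for patient characteristics as an exploratory extension, separate from step 1.

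**Cost.** Wording and one extra model, with no new patients, visits or measurements. The smallest Holm p-value faces 0.0125, where the detectable change is about 0.64 rather than 0.53 SD of the change. The joint test stays at 0.05. It shows that some change occurred without showing where, so the interval estimates are still needed.
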